##### Secondary outcomes

2.2.7.4

###### Positive emotion

2.2.7.4.1

Positive emotion will be assessed with the Positive and Negative Affect Schedule (PANAS (55)), a 20-item self-administered instrument that evaluates the frequency of positive and negative affective experiences. It consists of two 10-item subscales (positive and negative affect), each rated on a 5-point Likert scale ranging from 1 (“very slightly or not at all”) to 5 (“extremely”). The PANAS has demonstrated high internal consistency (α = .86–.90 for the Positive Affect subscale; α = .84–.87 for the Negative Affect subscale) and good convergent and discriminant validity across clinical and non-clinical populations, including university students.

###### Engagement

2.2.7.4.2

Engagement will be assessed with the Utrecht Work Engagement Scale–Student Version (UWES-S (56)), a 17-item self-administered instrument that measures vigor, dedication, and absorption. Items are rated on a 7-point Likert scale (0 = “never” to 6 = “always”). The UWES-S has shown good internal consistency (Cronbach’s α ranging from .80 to .90) and factorial validity in student populations.

###### Relationships

2.2.7.4.3

Relationships will be assessed with the Social Connectedness Scale (SCS (57)), an 8-item self-administered instrument that evaluates the degree of interpersonal closeness and belonging. Items are rated on a 6-point Likert scale (1 = “strongly disagree” to 6 = “strongly agree”), with higher scores reflecting stronger connectedness. The SCS has demonstrated excellent internal consistency (α = .91) and robust construct validity across diverse populations, including students.

###### Meaning

2.2.7.4.4

Meaning will be assessed with the Meaning in Life Questionnaire (MLQ (58)), a 10-item self-administered instrument with two subscales: presence of meaning and search for meaning. Each item is rated on a 7-point Likert scale (1 = “absolutely untrue” to 7 = “absolutely true”). The MLQ has demonstrated high internal consistency (α = .82–.88) and strong convergent and discriminant validity in both clinical and student samples.

###### Accomplishment

2.2.7.4.5

Accomplishment will be assessed with the Achievement Goal Questionnaire–Revised (AGQ-R (59)), a 12-item self-administered instrument that evaluates mastery-approach, mastery-avoidance, performance-approach, and performance-avoidance goals as indicators of achievement motivation. Items are rated on a 7-point Likert scale (1 = “not at all true of me” to 7 = “very true of me”). The AGQ-R has shown good internal consistency (α = .77–.90 across subscales) and has been validated in student populations, supporting its use in academic well-being research.

###### Satisfaction with the intervention

2.2.7.4.6

Satisfaction with the intervention will be assessed at post-intervention (T2) using the Client Satisfaction Questionnaire–8 (CSQ-8 (60); Vázquez et al. (61) for the Castilian Spanish version). The CSQ-8 is an 8-item self-administered instrument rated on a 4-point Likert scale, ranging from 1 to 4, with total scores ranging from 8 to 32, where higher scores indicate greater satisfaction. The original version has demonstrated excellent internal consistency (α >.90), while the Spanish validation confirmed high internal consistency (α = .83) and strong construct validity in clinical and research contexts.

##### Treatment adherence and dropouts

2.2.7.5

Throughout the study, information on participant dropouts will be systematically recorded, including the time point of withdrawal (T1, T2, or T3) and the stated reasons for discontinuation when available. Treatment adherence will be evaluated by tracking the number of modules completed within the mobile app and the between-session tasks performed by each participant (e.g., experiential exercises, reflections, and homework activities). For participants in the PPIA+M condition, adherence will also include attendance at the weekly 30-minute multiconference sessions. App data logs will automatically capture completion rates and activity engagement, while facilitators will maintain attendance and participation records for the multiconference sessions.

#### Data management

2.2.8

To protect participant confidentiality, all personal and clinical information will be anonymized through a coding system and stored separately from research data. Physical records will be numbered sequentially and preserved securely for five years following the completion of the study. Collected data will be entered into a secure database designed to exclude any direct personal identifiers. The research team will conduct regular quality control checks, including verification of data ranges and internal consistency, to ensure accuracy throughout the study. Access to both physical files and digital records will be restricted exclusively to authorized research personnel, safeguarded by password-protected systems and secure storage facilities. To prevent data loss, the database will be backed up systematically every 15 days. Finally, all study reports and resulting publications will be prepared in a way that guarantees participant anonymity, ensuring that no identifying information is disclosed.

#### Statistical analyses

2.2.9

Statistical analyses will be conducted using SPSS version 29.0 and R software (62), following the intention-to-treat (ITT) principle. All randomized participants will be analyzed in the groups to which they were assigned (PPIA, PPIA+M, WLCG), regardless of intervention adherence or dropout.

Missing data will be handled using multiple imputation by chained equations (MICE).

The imputation model will include the following predictors: sociodemographic characteristics (sex, gender identity, age, marital status, living arrangements, rural/urban setting, employment status, and self-reported socioeconomic level), academic variables (current academic program, year of enrolment), clinical characteristics (having initiated psychological or psychopharmacological treatment within the two months prior to the study, currently participating in another mental health–related research study), and baseline scores on the primary outcomes (emotional well-being and psychological, emotional, and social well-being).

To analyze the effect of the intervention on the primary outcome, psychological well-being, operationalized through two co-primary measures—global positive mental well-being assessed with the WEMWBS and emotional, psychological, and social well-being assessed with the MHC-SF—separate Linear Mixed Models (LMMs) will be conducted for each co-primary outcome using Restricted Maximum Likelihood (REML) estimation, with fixed effects for group, time, and the group-by-time interaction. Time will be treated as a categorical factor with three levels (T1: baseline, T2: post-intervention, T3: six-month follow-up), and random intercepts will be included to account for intra-subject variability. The baseline assessment (T1) will be modeled as part of the repeated outcome vector rather than as a separate baseline covariate. Random slopes for time will not be included in the primary models.

Model assumptions, including the normality and homoscedasticity of residuals, will be evaluated using Q-Q plots and residual-versus-predicted scatterplots before final model interpretation.

To control the family-wise Type I error rate across the two co-primary outcomes, a Bonferroni-adjusted significance threshold of α = .025 will be applied to the primary confirmatory group-by-time interaction test for each outcome. *Post hoc* pairwise comparisons among the three groups (PPIA vs. WLCG, PPIA+M vs. WLCG, and PPIA+M vs. PPIA) will be conducted using estimated marginal means at post-intervention (T2) and six-month follow-up (T3). Pairwise contrasts will be adjusted using the Bonferroni correction. Effect sizes will be calculated using Cohen’s *d* and interpreted as small (*d* < 0.50), moderate (*d* = 0.50–0.79), or large (*d* ≥ 0.80), following the guidelines proposed by Cohen (63).

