#### Eligibility criteria

2.2.2

Inclusion criteria include: (a) being an actively enrolled university student at the University of Santiago de Compostela (USC); and (b) having access to a smartphone with an internet connection. Exclusion criteria include: (a) having a current diagnosis of severe psychiatric disorder, including major depressive disorder with psychotic features, bipolar disorder, schizophrenia, severe cognitive impairment, dissociative disorders, active substance dependence, or active suicidal behaviors; (b) having started psychological or psychopharmacological treatment within the two months prior to the study or participating in another mental health-related study; (c) having insufficient proficiency in Spanish, or presenting sensory, cognitive, or physical impairments that would prevent engagement with the intervention; or (d) planning to move out of Galicia within the next 12 months.

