#### Sample size calculation

2.2.4

The sample size calculation was conducted using G*Power 3.1.9.7, selecting the F-test family and the “ANOVA: Repeated measures, within-between interaction” option. The calculation targeted the omnibus longitudinal group-by-time interaction in a design with three groups and three assessment points. The effect size was entered as Cohen’s *f* = 0.16, which represents a small effect and is approximately comparable to a standardized effect of *d/g* ≈ 0.32 under a simple two-group contrast approximation, based on prior meta-analytic findings that report small but consistent effects of app-based interventions on psychological well-being among university students (26). To account for the two co-primary outcomes, the alpha level was adjusted to α = .025 using a Bonferroni correction. The remaining parameters were statistical power = .95, correlation among repeated measures = .50, and nonsphericity correction *ϵ* = 1. Under these assumptions, the required analytical sample size was 141 participants, corresponding to 47 participants per group, with an actual power of .9509. To allow for an anticipated attrition rate of approximately 20%, the recruitment target was increased to 177 participants, corresponding to 59 participants per group.

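### The listed predictors for multiple imputation leave out randomized arm, so imputed follow-up scores carry no arm effect and the active-versus-waiting-list estimates shrink

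*Protocol article*

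**What the plan says.** Section 2.2.9 (Statistical analyses) commits to imputation: "Missing data will be handled using multiple imputation by chained equations (MICE"). It then sets out the model: "The imputation model will include the following predictors: sociodemographic characteristics (sex, gender identity, age, marital status, living arrangements, rural/urban setting" and further sociodemographic, academic and clinical baseline items, closing with "and baseline scores on the primary outcomes (emotional well-being and psychological, emotional, and social well-being"). The list is itemised, gives no sign that its items are only examples, and is not deferred to another document. Neither arm nor any T2 or T3 score appears in it.

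The same section defines the analysis set, "All randomized participants will be analyzed in the groups to which they were assigned", and the primary mixed model, "with fixed effects for group, time, and the group-by-time interaction". Section 2.2.4 (Sample size calculation) supplies the expected amount of missing data: "To allow for an anticipated attrition rate of approximately 20%, the recruitment target was increased to 177 participants", "corresponding to 59 participants per group".

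**The concern.** An imputation model should contain at least the terms that the analysis model tests. Here the analysis asks whether the arms diverge over time, while the imputation draws each missing follow-up score from a distribution shared by all arms given baseline. Every imputed score is thus pulled toward the average of the arms, whichever arm the participant belongs to, and is then analysed under that participant's own arm.

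The omnibus group-by-time test, which is the confirmatory test for each co-primary outcome, and all three pairwise comparisons are affected. The main harm is an understated benefit over the waiting list and a higher risk of missing a real effect. For PPIA+M versus PPIA the error can also create a difference that does not exist.

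**Working it through.** **Inputs.** From section 2.2.4: f = 0.16, described there as comparable to d ≈ 0.32; α = .025; three groups and three visits; correlation .50; analytical N = 141; 177 recruited, 59 per group; attrition about 20%. Assumed, because the article does not give them: the split of attrition by visit and arm, dropout completely at random, and equal true effects of 0.32 in both active arms.

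**The plan's own figure.** For the within-between interaction, λ = f²·N·3/(1 − .50), df1 = (3 − 1)(3 − 1) = 4 and df2 = (N − 3)(3 − 1). With N = 141, λ = 0.0256 × 141 × 6 = 21.66 and df2 = 276, which gives power .951 (stated .9509). For attrition, 141/0.80 = 176.25, rounded up to 177. Both figures reproduce.

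**Bias without arm.** Let m_a be the missing fraction in arm a and δ_a its true effect, with zero for the waiting list. Randomization balances baseline in expectation, so an imputed score has expected effect μ = Σ(1 − m_a)δ_a / Σ(1 − m_a) in every arm. The analysed mean effect in arm a is (1 − m_a)δ_a + m_a·μ. An active-versus-waiting-list contrast therefore has expectation

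(1 − m_a)δ_a + (m_a − m_0)μ.

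*Equal missingness m.* The second term vanishes and the contrast is (1 − m)δ:
- m = 10%: 0.90 × 0.32 = 0.288
- m = 20%: 0.80 × 0.32 = 0.256
- m = 30%: 0.70 × 0.32 = 0.224

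In simulation (59 per arm, correlation .5, 20% missing in every arm) the estimate was about 0.26 without arm and 0.32 with arm. If dropout is staggered at 10% by T2 and 20% by T3, the simulated values without arm were 0.289 at T2 and 0.256 at T3.

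*Unequal missingness (assumed; order WLCG/PPIA/PPIA+M).*

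| Missing | μ | PPIA vs WLCG | PPIA+M vs WLCG | PPIA+M vs PPIA (true 0) |
|---|---|---|---|---|
| 10/25/25% | 0.200 | 0.270 | 0.270 | 0 |
| 10/30/20% | 0.200 | 0.264 | 0.276 | +0.012 |
| 10/35/10% | 0.202 | 0.259 | 0.288 | +0.029 |
| 10/10/35% | 0.202 | 0.288 | 0.259 | −0.029 |

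For example, the PPIA entry for 10/35/10% is 0.65 × 0.32 + 0.25 × 0.202 = 0.208 + 0.051 = 0.259. By formula the active-versus-waiting-list contrasts shrink by 10% to 19%; allowing for simulation error, about 9% to 20%. PPIA+M versus PPIA moves in either direction, according to which arm loses more participants.

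**Effect on the omnibus test, as a guide.** Shrinking f by 20% gives 0.16 × 0.80 = 0.128, and 0.128² = 0.016384.
- N = 141: λ = 0.016384 × 141 × 6 = 13.86, power .783.
- N = 177: λ = 0.016384 × 177 × 6 = 17.40, power .886. This counts imputed scores as fully observed, so it is an upper guide.

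**The case against.** The text says what the model will include, not that it includes nothing else, and a journal article condenses a longer plan. This carries real weight for the follow-up scores. Chained equations commonly let incomplete variables predict one another, so T2 and T3 may enter as imputation targets without being listed. A reader might infer that T2 is never used to impute T3, or the reverse; the article does not say so. The argument is weaker for arm: it is complete, so it would not enter as a target, and it is the obvious item to name in so detailed a list. Nor does using T2 to predict T3 cure its absence. With staggered dropout and no arm term, the simulated T3 contrast was 0.267 and T2 stayed at 0.29.

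A reader might also infer that every contrast shrinks by the missing fraction. That needs equal missingness, and it fails for PPIA+M versus PPIA, as the table shows. Unequal dropout is plausible, since the Discussion expects better adherence in PPIA+M.

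The error is conservative against the waiting list: if no arm has an effect, the formula gives zero for every contrast, so it creates no spurious omnibus effect. That limits the harm but does not remove it.

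Finally, two listed predictors repeat exclusion criteria ("having started psychological or psychopharmacological treatment within the two months prior to the study or participating in another mental health-related study") and should be nearly constant among those randomized. A reader might take this for a source of bias. It is not; they are merely uninformative.

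**Conclusion.** The point stands for randomized arm. The published predictor list omits it, nothing else in the article supplies it, and following the list biases the primary estimates. At the anticipated 20% attrition, equal across arms, d = 0.32 is estimated at about 0.26. Omnibus power at α = .025 is then about .78 at N = 141 and at most about .89 at N = 177, against the stated .95, so the attrition allowance does not restore the planned power. The exact size depends on how attrition falls by visit and arm, which is assumed here, as are dropout completely at random and equal effects in the active arms. The documents do not support a claim that follow-up scores are definitely excluded from the imputation, or that all contrasts are always pulled toward zero. Since the fault touches the primary estimate at the protocol's own attrition rate, it should be corrected before follow-up data are analysed.

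**What to change.** In section 2.2.9, add randomized arm to the imputation model, or state that imputation is run separately by arm. State also that T1, T2 and T3 scores of both WEMWBS and MHC-SF are in the model. The first change removes the bias: with arm included, the simulated contrast returned to 0.32. The second keeps the information in the observed follow-up scores and makes missing-at-random more credible when dropout depends on T2.

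Fitting the REML mixed models directly to all observed T1 to T3 scores is an acceptable alternative, not a requirement. It relies on the random-intercept covariance structure and would not use the listed background variables, so imputation with arm included remains a legitimate choice. The two predictors that duplicate exclusion criteria can be dropped for tidiness.

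The cost is a sentence or two in one paragraph. No new data, participants or assessments are needed.

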To our knowledge, this is the first randomized controlled trial to evaluate a fully PERMA-based psychological intervention delivered via a mobile application in university students, and to directly compare a self-guided app format with a blended format that incorporates synchronous group-based telephone support. By examining not only efficacy but also adherence, satisfaction, and mechanisms of change across PERMA dimensions, this study addresses critical gaps in the digital mental health literature regarding engagement and scalability of positive psychology interventions in higher education contexts. The primary objectives of this randomized controlled trial are to: (a) assess the efficacy of a positive psychology–based psychological intervention grounded in the PERMA model in promoting psychological well-being among university students administered through a smartphone app, with (PPIA + M) and without the addition of telephone multiconference calls (PPIA), compared to a waiting list control group (WLCG); and (b) examine the mediators and moderators of change in psychological well-being. The central hypotheses are that participants in both the PPIA and PPIA+M groups will demonstrate significantly greater improvements in psychological well-being compared to the WLCG at post-treatment and 6-month follow-up, with the PPIA+M group showing more pronounced improvements due to the added telephone support; additionally, it is expected that the change in positive emotion, engagement, relationships, meaning, and accomplishment will mediate the effects of both interventions; and that sociodemographic, academic, and clinical variables, as well as satisfaction with the intervention, will moderate treatment effects. Mediation and moderation analyses are planned as exploratory and hypothesis-generating, aimed at informing future optimization of the intervention.

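### The pairwise T2 and T3 contrasts come from a model with free arm means at T1, so they are not baseline-adjusted and lose precision (25% of the variance at the protocol's correlation of .50)

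*Protocol article*

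**What the plan says.** All on this point is in the protocol article. Under Statistical analyses (2.2.9), each co-primary outcome (WEMWBS, MHC-SF) gets a REML linear mixed model "with fixed effects for group, time, and the group-by-time interaction", with time as a three-level factor and a random intercept. On baseline: "The baseline assessment (T1) will be modeled as part of the repeated outcome vector rather than as a separate baseline covariate". On covariance: "Random slopes for time will not be included in the primary models". No constraint that the arms share a T1 mean is stated.

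The same section sets the hierarchy: "a Bonferroni-adjusted significance threshold of α = .025 will be applied to the primary confirmatory group-by-time interaction test for each outcome". The three between-arm comparisons are labelled post hoc and "will be conducted using estimated marginal means at post-intervention (T2) and six-month follow-up (T3"). For multiplicity: "Pairwise contrasts will be adjusted using the Bonferroni correction". The size of that Bonferroni family is not given.

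The central hypotheses in the Introduction are arm-specific and visit-specific. Both active arms are expected to show "significantly greater improvements in psychological well-being compared to the WLCG at post-treatment and 6-month follow-up", with PPIA+M ahead of PPIA. The Sample size calculation (2.2.4) assumes "statistical power = .95, correlation among repeated measures = .50, and nonsphericity correction" of 1, with f = 0.16 (given as d or g of about 0.32), α = .025 and 141 analysed participants (47 per arm).

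**The concern.** With group, time and group-by-time all free, the model has nine unconstrained cell means. A between-arm contrast of estimated marginal means at T2 then takes its information from the T2 scores only. Under Design (2.1), randomization follows the baseline assessment, so true T1 means are equal by design, and the model does not use this fact.

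Two things are at stake. The first is precision: confidence intervals for the pairwise effects are wider than the collected data require. The second is coherence within the sample: the interaction test works on change from baseline while the follow-up contrasts compare levels. Chance imbalance at T1 can therefore push the two apart, and a Cohen's d computed from these contrasts carries the imbalance with it. The omnibus interaction cannot say which arm differs or when, so the arm-specific hypotheses depend on these contrasts.

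**Working it through.** **Inputs.** ρ = .50, ε = 1, f = 0.16, d ≈ 0.32, α = .025, 47 analysed and 59 recruited per arm (2.2.4); model terms and contrasts (2.2.9). Variances below are in units of σ², with equal variance and correlation at all visits, which is what a random intercept implies.

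**1. The plan's own figure.** λ = f²·N·m/(1−ρ) = 0.0256 × 141 × 3 / 0.5 = 21.66; df1 = 2 × 2 = 4; df2 = 138 × 2 = 276. At α = .025 power is .951 at N = 141 and .946 at N = 138, so 141 is reproduced. With 20% attrition, 141/0.8 = 176.25, giving 177, and 47/0.8 = 58.75, giving 59 per arm.

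**2. Contrast as planned.** Variance = 2/n = 2/47 = 0.0426, SE 0.206 SD. In 40 simulated REML random-intercept fits on complete data, the T2 contrast matched the raw T2 mean difference to within 7 × 10⁻¹⁶. The mean model SE was 0.205.

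**3. Contrast with a common T1 mean (or baseline as covariate).** Variance = 2(1−ρ²)/n = 1.5/47 = 0.0319, SE 0.179 SD. The ratio is 0.75. With 59 per arm and no loss, SE goes from 0.184 to 0.159. Since 47 × 0.75 = 35.25, about 35 per arm with adjustment would match the planned contrast at 47.

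**4. Dependence on ρ.** The value .50 is a planning assumption, so the range matters. Variances are relative to the planned contrast:

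| ρ | Change-score contrast, 2(1−ρ) | Baseline-adjusted, 1−ρ² | Reduction from adjustment |
|---|---|---|---|
| .3 | 1.40 | 0.91 | 9% |
| .4 | 1.20 | 0.84 | 16% |
| .5 | 1.00 | 0.75 | 25% |
| .6 | 0.80 | 0.64 | 36% |
| .7 | 0.60 | 0.51 | 49% |

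At ρ = .50, replacing the contrasts by differences in change would recover nothing.

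**5. Chance imbalance.** The T1 difference between two arms has SD √(2/47) = 0.206, and the fraction ρ = .50 of it carries into the T2 contrast (simulated correlation 0.50). A one-SD imbalance moves the estimate by 0.5 × 0.206 = 0.103 SD, about a third of 0.32.

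**6. Illustrative power for one contrast.** With d = 0.32, 47 per arm, two-sided:
- α = .025: .245 as planned, .326 adjusted.
- α = .025/3 (assumed family of three): .139 as planned, .198 adjusted.

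**7. The confirmatory test.** For effects (δ₂, δ₃) at T2 and T3 and ρ = .50, the covariance of the two visit effects is proportional to [[1, .5], [.5, 1]] when based on change, and to [[.75, .25], [.25, .75]] under a common T1 mean. For equal effects, the quadratic form δ′V⁻¹δ is 1.33 against 2.00, a ratio of 0.67. For a T2-only effect it is 1.33 against 1.50, a ratio of 0.89.

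**The case against.** The strongest reply is that nothing here is invalid. Each contrast is unbiased over randomizations, its standard error already covers chance imbalance, and Type I error is preserved. The model also matches the interaction for which the trial was sized, and that calculation reproduces. All of this stands.

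A reader might infer several stronger things that the document does not support:

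- *That the primary analysis ignores baseline.* It does not. The confirmatory test is the group-by-time interaction, which uses T1 through within-person change. The contrasts are labelled post hoc.
- *That putting T1 in the outcome vector is the error.* It is not, and one of the two remedies keeps it there. The loss comes from the free group effect at T1 combined with visit-specific marginal means.
- *That baseline plays no part at all.* This is exact only for the contrast within a complete or imputed dataset. About 20% attrition is expected, and the imputation model includes baseline scores on both co-primary outcomes, so baseline does shape the imputed T2 and T3 values.
- *That the contrasts and the interaction have different estimands.* Under randomization, the difference in level and the difference in change share one expectation. They can disagree only by chance in a sample.
- *That the gain is a fixed quarter, or that it rescues the pairwise power.* The gain depends on ρ and falls to 9% at .3. The illustrative power stays low after adjustment.

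**Conclusion.** The point holds as an efficiency defect in the contrasts that carry the arm-specific hypotheses. It is not an error of validity. Adjusting for baseline reduces their variance by ρ², which is 25% at the protocol's own ρ = .50 (planned variance 33% larger than needed, SE 15% larger) and between 9% and 49% for ρ from .3 to .7. These figures assume compound symmetry and complete data. The power figures also rest on the document's approximation d ≈ 0.32, and the second pair on an assumed family of three contrasts. Because randomization comes after T1, the equal-baseline assumption needed for the gain is guaranteed by the design. The same constraint also strengthens the confirmatory test.

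**What to change.** Under Statistical analyses, keep T1 in the outcome vector but give it one mean common to all arms: time effects plus arm × T2 and arm × T3 terms, with no arm effect at T1. Alternatively, model T2 and T3 as outcomes with the baseline score as covariate. Take two things from that one model: the confirmatory test, as the joint 4-df test of the arm effects at T2 and T3 at α = .025 per co-primary outcome, and the pairwise contrasts with their effect sizes.

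No new data are needed. The cost is wording. The model terms, the name of the confirmatory test and the description of the contrasts in 2.2.9 must be changed together, because the present group-by-time label would no longer describe the test exactly. The sample size in 2.2.4 need not be recalculated: with respect to this change it is conservative.

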### Design

2.1

A randomized controlled trial (RCT) will be conducted. The present trial protocol follows the CONSORT (36) and SPIRIT (37) statements’ extensions for clinical trials, ensuring the inclusion of all key methodological aspects. Participants will be randomly assigned to one of three groups: (a) an app-based positive psychology–based psychological intervention grounded in the PERMA model (PPIA; experimental group 1); (b) an app-based positive psychology–based psychological intervention grounded in the PERMA model supplemented by telephone multiconference calls (PPIA+M; experimental group 2); or (c) a waiting list control group (WLCG).

The study phases are illustrated in **Figure 1**, which depicts the flow of participants through the trial. Assessments will be conducted at three time points across the three groups: pre-intervention (T1), post-intervention (T2), and follow-up at 6 months (T3). After the baseline assessment, eligible participants will be randomized, and interventions will be administered over five weeks. The post-intervention assessment will be conducted immediately after completion, followed by a follow-up evaluation at 6 months. To ensure participant retention and limit attrition, strategies recommended in clinical research design will be employed. These include clear communication of expectations, structured reminder systems, brief follow-ups in case of missing data, and offering flexible scheduling for phone-based sessions in the PPIA+M group. The intervention app will be designed for ease of use to support consistent engagement (38).

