#### Exit strategy

2.2.10

An exit strategy will be implemented in two key scenarios: (1) when a participant decides to withdraw from the study prematurely, and (2) at the official conclusion of the trial. In cases of premature withdrawal, a voluntary exit phone call will be conducted to document the reasons for leaving through a structured questionnaire. At the end of the study period, which includes a five-week intervention period followed by a six-month follow-up, participants will be informed about the transition and closure of the research.

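### The primary mixed model assumes equal variances and correlations across unevenly spaced visits, so the .025 group-by-time test may be anti-conservative if the correlations differ

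*Protocol article*

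**What the plan says.** The Statistical analyses section (2.2.9) plans a separate linear mixed model for each co-primary outcome, "using Restricted Maximum Likelihood (REML) estimation, with fixed effects for group, time, and the group-by-time interaction". On the time scale it states "Time will be treated as a categorical factor with three levels", and on baseline "The baseline assessment (T1) will be modeled as part of the repeated outcome vector rather than as a separate baseline covariate". The covariance part is given in two statements: "random intercepts will be included to account for intra-subject variability" and "Random slopes for time will not be included in the primary models". No residual covariance structure, robust standard error or sphericity correction is named. The assumption checks are Q-Q plots and plots of residuals against predicted values.

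The confirmatory test is taken from this model: "a Bonferroni-adjusted significance threshold of α = .025 will be applied to the primary confirmatory group-by-time interaction test for each outcome". Pairwise group differences in estimated marginal means at T2 and T3 follow as Bonferroni-adjusted post hoc contrasts.

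The Exit strategy section describes the study period as one "which includes a five-week intervention period followed by a six-month follow-up". The Sample size calculation section uses a single correlation of .50 for all visit pairs and a nonsphericity correction of 1, which is the same covariance assumption.

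**The concern.** A random intercept with independent, equal-variance residuals gives every visit the same variance and every pair of visits the same correlation. The two intervals here differ about five-fold, and scores taken five weeks apart will normally agree more closely than scores taken six months or more apart. Because T1 is part of the outcome vector, all three correlations enter the group-by-time test.

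When variances of the differences between visits are unequal (sphericity fails), the uncorrected interaction test uses too many degrees of freedom and rejects too often under the null. The protocol splits alpha between two co-primary outcomes in order to hold the family-wise rate at .05. If each test runs above .025, that bound is lost. Q-Q and residual-versus-predicted plots show distribution and spread but not the correlation between a participant's own visits, and no alternative is named in case the assumption fails.

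**Working it through.** **Inputs from the protocol.** Three groups, three visits, f = .16, correlation .50, nonsphericity correction 1, alpha .025, 141 analysed (47 per group), 177 recruited (59 per group). The documents give no visit-specific SDs or correlations, so those below are assumptions, shown as a range.

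**1. The plan's own figure.**
- Noncentrality: λ = f²·N·m/(1 − ρ) = .0256 × 141 × 3/.5 = 21.66.
- Degrees of freedom: (3 − 1)(3 − 1) = 4 and (141 − 3)(3 − 1) = 276.
- Power at alpha .025 is .95097, against the stated .9509.
- 141/.8 = 176.25, which becomes 177 with equal groups of 59.

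The sample size reproduces, under compound symmetry.

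**2. Null rejection rate of the confirmatory test.** On complete balanced data the random-intercept REML interaction test equals the uncorrected repeated-measures F test (when the intercept variance estimate is positive). Let T be the 2×2 covariance of the two orthonormal time contrasts, (y1 − y2)/√2 and (y1 + y2 − 2y3)/√6. Then ε = (tr T)²/(2·tr T²).

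Example for (T1T2, T2T3, T1T3) = (.7, .5, .4) with equal SDs of 1:
- T11 = 1 − .7 = .300
- T22 = (6 + 1.4 − 1.6 − 2.0)/6 = .633
- T12 = 2(.5 − .4)/√12 = .058
- ε = .933²/(2 × .498) = .875

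Under the null, the F statistic is a ratio of weighted chi-squares, with weights equal to the eigenvalues of T. Simulating that ratio (4 million draws per case, 47 per arm) gives:

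| Assumed correlations (T1T2, T2T3, T1T3), equal SDs | ε | Rejection at nominal .025 |
|---|---|---|
| .5, .5, .5 (compound symmetry) | 1.000 | .025 |
| .6, .5, .4 | .949 | .028 |
| .7, .5, .4 | .875 | .032 |
| .8, .5, .4 | .765 | .039 |
| .8, .4, .3 | .728 | .042 |

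Smaller separate simulations of the mildest unequal case gave .027 to .0285, hence the range of about .027 to .042. Results at 59 per arm are practically the same. The two-outcome Bonferroni bound becomes 2 × .027 = .054 to 2 × .042 = .084, in place of .050.

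**3. The planned T3 contrasts.** The model computes the standard error of a between-group difference at T3 from the total variance averaged over visits. The correlations do not enter.
- With equal SDs, coverage of the nominal 95% interval is 95.0% (to within simulation error) in every correlation scenario above.
- With SDs 1/1.1/1.25 in all arms, the average variance is (1 + 1.21 + 1.5625)/3 = 1.2575 and the T3 variance is 1.5625. The ratio is 1.243, so the true standard error is √1.243 = 1.115 times the one used. The critical value 1.96 acts as 1.96/1.115 = 1.76, and the two-sided error is about .08 at nominal .05.
- With SDs 1/1.05/1.1, coverage is 93.8%.

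**4. The alternative.** The unstructured-covariance test (Wilks, exact F) rejected at .0245 to .0252 in the four covariances tried: compound symmetry, (.6, .5, .4), (.8, .5, .4), and (.7, .5, .4) with SDs 1/1.1/1.3. If compound symmetry is true, its power at N = 141 is .947 to .950, against .951 for the random-intercept test.

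**The case against.** **The residual structure may be named elsewhere.** Independence is an inferred default, and a full analysis plan that is not shown could pair the random intercept with another residual structure. That is fair. But the article sets out the covariance part of the primary model, rules out one way of relaxing it and plans its sample size on the same assumption, so compound symmetry is the natural reading.

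**The departure is unknown.** A reader might infer that the confirmatory test has the wrong error rate. The documents do not support that: they contain no visit-specific correlations or SDs, the test is exact under sphericity, and a mild departure moves it only to about .027 or .028.

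**T3.** A reader might also infer that uneven spacing makes the T3 intervals too narrow. It does not. The planned T3 comparisons are between-group differences in marginal means, which do not depend on the correlations. A change-from-baseline contrast would, but the protocol does not list one. The figure of about .08 needs a T3 variance above the visit average in all arms. If uneven response raised the SDs (1/1.1/1.25) in the treated arms only, the T3 error for PPIA against waitlist would be about .061 at nominal .05. A common unstructured matrix would not fully repair that case: about .063 for PPIA+M against PPIA and .044 for PPIA against waitlist.

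**Random slopes.** A reader might take their exclusion as the defect. With categorical time and one observation per visit, a full set of random time effects cannot be separated from the residual, so leaving them out is defensible. The gap is the residual covariance.

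**Missing data.** The calculations use complete data. The protocol plans multiple imputation and expects about 20% attrition; behaviour after pooling was not examined.

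**Conclusion.** The point holds in conditional form. The primary model, on its natural reading, rests on compound symmetry across visits about five weeks and six months apart. The planned diagnostics do not test the correlation pattern, and no alternative is named. If the correlations differ, the confirmatory test may be anti-conservative, at about .027 to .042 against .025 over the assumed range, and it is exact if sphericity holds. The T3 marginal-mean intervals are at risk only if variance at T3 exceeds the visit average.

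The change is worth making because the error falls on the confirmatory test, runs toward false positives and is cheap to prevent. Confidence is medium: the size rests on assumed correlations, complete data and an inferred residual structure.

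**What to change.** In the Statistical analyses section, make the primary model for each co-primary outcome a REML model with fixed effects for group, categorical time and their interaction, an unstructured 3×3 residual covariance in place of the random intercept, and Kenward-Roger degrees of freedom. Keep the random-intercept model as the pre-specified fallback if the unstructured model does not converge. State this before outcome data are seen.

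The cost is one line of specification and four more covariance parameters (six against two). If compound symmetry is true, the loss is at most about 0.5 points of power (.951 to .947 at N = 141), so the sample size needs no material change.
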